### Safety

Adverse events and serious adverse events will be summarized per treatment group and descriptively compared between treatment-groups with a Chi-Square test.

Secondary endpoints:

Secondary analyses will investigate the relapse rate (new antibiotic treatment needed for AE-COPD within six months), time to relapse, the treatment effect with respect to clinical cure rates and failure rates at end-of-treatment (EOT)-visit and the TOC-visit in the modified ITT (mITT) population and the clinical evaluable (CE)-population. Exacerbation rates and time to next exacerbation will be assessed within 1 year after the index exacerbation.

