**Methods/Design:**

A total of 980 patients with moderate acute exacerbations will be included in 22 German centers (hospitals and private practices). Patients will receive a standardized treatment for exacerbation including systemic corticosteroids, inhaled bronchodilators and supplementary oxygen if needed and will be randomized to additional treatment with placebo or antibiotic (oral sultamicillin) for five days.

The primary endpoint is clinical failure defined by need for additional antibiotic treatment until day 30. Secondary endpoints will assure that management of AE-COPD without antibiotics does not result either in increased occurrence of relapse, new exacerbations, prolonged recovery, or unwanted long-term consequences.

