## Background

Antibiotic resistance is increasing in hospitals as well as in the community. It has been shown that antibiotic prescriptions without a clear indication contribute significantly to this increase [1]. Acute exacerbations of COPD (AE-COPD) represent a frequent clinical situation in which administration of antibiotics is considered. In 2010 nearly 700.000 hospital discharges for COPD in the U.S. [2] have been registered. A retrospective cohort study identified that antibiotics were prescribed in 85% of 69 820 patients admitted for acute exacerbations of COPD to 360 hospitals throughout the United States [3]. This is impressive as evidence of efficacy of antibiotic treatment of AE-COPD is scarce. It is estimated that about 70% of exacerbations are infectious in origin [4]. However, only 20-30% are associated with detection of bacteria by sputum culture [4]. Importantly, detection of pathogens by culture is not per se a proof of infection. Particularly in COPD patients growth of bacteria in sputum cultures can also result from colonization of the airways [5]. Up to now colonization is not considered as a clear indication for antibiotic treatment. In addition, others and we have shown that respiratory viruses are detected in more than 50% of exacerbations and also have to be considered as major infectious triggers [6, 7]. In viral infections antibiotic therapy is not expected to be effective [8]. Moreover antibiotic treatment is associated with increased morbidity, mainly reflected by gastro-intestinal complications such as diarrhoea, often caused by C. difficile [9].

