A recent Cochrane review assessed the effects of antibiotics in the management of acute COPD exacerbations on treatment failure as observed between seven days and one month after treatment initiation (primary outcome) and on other patient-important outcomes (mortality, adverse events, length of hospital stay) [10]. In this most recent systematic review using GRADE methodology [11] 16 trials with 2068 participants were included. Outpatients were considered to have mild to moderate exacerbations. Only the most recent trial showed a benefit of antibiotic treatment and drove the results towards beneficial effects of antibiotics [12]. When the meta-analysis was restricted to currently available drugs however, there was no significant benefit but just a trend in favour of antibiotics (RR 0.80; 95% CI 0.63 to 1.01; I2 = 33%) [10]. However, evidence of high quality showed that antibiotics significantly reduced the risk of treatment failure in inpatients with severe exacerbations (ICU not included) (RR 0.77; 95% CI 0.65 to 0.91; I2 = 47%) regardless of whether restricted to current drugs or not. There still is only one trial with 93 patients admitted to the ICU, which was also analysed in this review [13]. This trial showed a large and statistically significant effect on treatment failure (RR 0.19; 95% CI 0.08 to 0.45; high-quality evidence) [10]. In studies addressing mortality evidence of low-quality from four trials in inpatients showed virtuality no effect of antibiotics on mortality (Peto OR 1.02; 95% CI 0.37 to 2.79) [10]. Length of hospital stay (in days) was similar in the antibiotics and placebo groups except for the ICU study. The overall incidence of adverse events was higher in the antibiotics groups (Peto OR 1.53; 95% CI 1.03 to 2.27). Patients treated with antibiotics experienced more diarrhoea based on three trials (Peto OR 2.62; 95% CI 1.11 to 6.17; high-quality evidence) [10]. The authors concluded on the basis of these findings that for outpatients and inpatients the results were inconsistent. The risk for treatment failure was significantly reduced in both inpatients and outpatients when all trials (1957 to 2012) were included but not when the analysis for outpatients was restricted to currently used antibiotics. Also, antibiotics had no statistically significant effect on mortality and length of hospital stay in inpatients and almost no data on patient-reported outcomes exist [10]. The appraisal of the results of this systematic review is largely impaired by the fact that there was no pre-defined standard treatment of AE-COPD including corticosteroids, even not in the most recent trials. Therefore it is impossible to judge the benefit of antibiotic treatment in addition to standard treatment of AE-COPD.

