### Sample size calculation

A limited number of studies have compared antibiotic treatment to placebo in patients with AE-COPD. Jorgensen et al. [20] found in 1992 a 63% success rate with placebo as compared to 64% with Amoxicillin after 7 days of treatment of uncomplicated exacerbations of chronic bronchitis. In contrast Anthonisen et al. [21] found in 1987 a 55% success rate with placebo and a 68% response rate with antibiotic treatment for 10 days. Daniels et al. [15] observed in 2010 a clinical success in the first study using a standardized treatment including systemic corticosteroids in 61% of patients from the doxycycline group and 53% from the placebo group. In all these studies background standard of care has not been optimized and it is assumed that this is the reason for observed differences in small studies. It is thus assumed that the response rate in the study population will be in the order of 65%. With a one-sided type 1 error of 2.5% 479 patients per group have to be recruited to reject the null-hypothesis of relevant inferiority of placebo treatment with 90% power and a non-inferiority margin of 10%. (Sample-size calculation has been performed with nQuery-Advisor 7.0).

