If the primary study outcome is met the community will benefit from reduced consumption of antibiotics. The study will include 960 patients and will be sufficiently powered to precisely estimate a potential risk from waiving anti-biotic treatment and to definitively answer this crucial clinical question.

A limited number of studies have compared antibiotic treatment to placebo in patients with AE-COPD. Jorgensen et al. [20] found in 1992 a 63% success rate with placebo as compared to 64% with Amoxicillin after 7 days of treatment of uncomplicated exacerbations of chronic bronchitis. In contrast Anthonisen et al. [21] found in 1987 a 55% success rate with placebo and a 68% response rate with antibiotic treatment for 10 days. Daniels et al. [15] observed in 2010 a clinical success in the first study using a standardized treatment including systemic corticosteroids in 61% of patients from the doxycycline group and 53% from the placebo group. In all these studies background standard of care has not been optimized and it is assumed that this is the reason for observed differences in small studies. It is thus assumed that the response rate in the study population will be in the order of 65%. With a one-sided type 1 error of 2.5% 479 patients per group have to be recruited to reject the null-hypothesis of relevant inferiority of placebo treatment with 90% power and a non-inferiority margin of 10%. (Sample-size calculation has been performed with nQuery-Advisor 7.0).

The trial is designed and powered to prove that antibiotic therapy is not necessary in addition to standard of care in patients with moderate AE-COPD with the aim to reduce unnecessary antibiotic prescriptions and the ultimate goal to reduce antibiotic resistance. This is the first study in the field to use a non-inferiority trial design including a placebo arm. Other trials have used superiority design for antibiotics and yielded inconclusive results. These trials were all designed with the hypothesis that antibiotic therapy should be superior to placebo. In this trial we will investigate whether use of placebo is not inferior to antibiotic treatment and have chosen a tight non-inferiority margin to justify that antibiotic treatment should be withheld in this patient population in the future. This is clinically relevant for the target population as adverse effects and antibiotic resistance could be decreased if antibiotic treatment will be shown not be necessary in this trial.

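### The only between-arm safety comparison named is a chi-square test, which puts no limit on the excess risk of placebo; report risk differences with 95% confidence intervals (minor point)

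*Protocol article*

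**What the plan says.** The Safety paragraph of the statistical section in the protocol article names one between-arm method: "Adverse events and serious adverse events will be summarized per treatment group and descriptively compared between treatment-groups with a Chi-Square test". It mentions no effect estimate, confidence interval or margin for a safety outcome.

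The section on key safety criteria lists four items: adverse events, serious adverse events, complications (intensive care, ventilatory support) and vital status. The Safety paragraph names a comparison for the first two only.

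Other outcomes that bear on the risk of withholding antibiotics have their own place. The abstract says: "Secondary endpoints will assure that management of AE-COPD without antibiotics does not result either in increased occurrence of relapse, new exacerbations, prolonged recovery". The statistical section adds: "Secondary analyses will investigate the relapse rate (new antibiotic treatment needed for AE-COPD within six months), time to relapse".

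The primary endpoint is treated differently. Under Efficacy/test accuracy, a two-sided 95% interval for the difference in failure rates, placebo minus antibiotic, is compared with 10%. The Discussion explains that the aim is to demonstrate that differences between the strategies are irrelevant.

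**The concern.** A test of difference and a claim of no relevant harm ask opposite questions. A large p-value means only that the data did not exclude zero difference; it does not say how large a difference they leave open. The protocol applies this reasoning to its primary endpoint. The safety comparison, as written, does not follow it.

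This matters most for uncommon, serious events. Treatment failure and relapse are both defined by need for antibiotic therapy, and cure by diary cards. Intensive care, ventilation and death appear as outcomes in their own right only among the safety criteria. If the arms are compared on serious events by a p-value alone, the report will probably show non-significance even if placebo carries a real excess, and it will give no upper limit on that excess. A reader deciding whether antibiotics can be withheld needs that limit.

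**Working it through.** **Plan's own figure.** "With a one-sided type 1 error of 2.5% 479 patients per group have to be recruited to reject the null-hypothesis of relevant inferiority". Inputs from Sample size calculation: response 65% in both arms, margin 10 points, one-sided 2.5%, power 90%.

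n per arm = (1.960 + 1.282)² × 2 × 0.65 × 0.35 / 0.10² = 478.1, rounded up to 479. The stated figure reproduces exactly. It concerns the primary endpoint; no figure is stated for safety.

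**Inputs for safety.** 960 patients analysed (Study populations), taken as 480 per arm; equal allocation is an assumption consistent with 479 per group. The article gives no adverse event or serious adverse event rates for this trial, so every rate below is an assumption, shown as a range.

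**Power of the chi-square test** (two-sided 5%, no continuity correction):

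- SE0 = √[2 p̄(1 − p̄)/480], with p̄ the mean of the two rates
- SE1 = √[(p1(1 − p1) + p2(1 − p2))/480]
- Power = Φ[(|p2 − p1| − 1.960 × SE0)/SE1]

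For 2% versus 4%: SE0 = √(2 × 0.03 × 0.97/480) = 0.01101 and SE1 = √((0.0196 + 0.0384)/480) = 0.01099. The argument is (0.02 − 0.02158)/0.01099 = −0.144, so power is 44%.

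| Assumed rates | Power |
|---|---|
| 1% vs 2% | 25% |
| 2% vs 4% | 44% |
| 5% vs 8% | 47% |
| 10% vs 15% | 65% |
| 5% vs 10% | 84% |

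A doubling from a 1% or 2% base is missed more often than found. A doubling from 5% would usually be seen.

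**What an interval adds.** Suppose 4% on placebo and 2% on antibiotic are observed. The test statistic is 0.02/0.01101 = 1.82, so p is about 0.07. The Wald 95% interval is 0.02 ± 1.960 × 0.01099, or about −0.2 to +4.2 points. The p-value alone says not significant; the interval says an excess of about 4 points on placebo is not excluded.

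**If the observed rates are equal**, the half-width is 1.960 × √[2p(1 − p)/480]: about 1.8 points at 2%, 2.8 at 5% and 3.8 at 10%. The trial can therefore report informative limits if it plans to.

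**The case against.** The strongest reply is that the comparison is labelled descriptive and no safety conclusion is tied to its p-value. Reading non-significance as safety would be a reader's mistake, not a rule of the plan. This is also a journal article. Tabulation of events by type and methods for individual safety items commonly sit in the full protocol or analysis plan, and nothing stops intervals from being reported beside the test. This largely stands, and it is why the point is minor. It does not remove the point, because the article does fix a method and that method does not fit the objective.

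The Discussion's claim that the study is "sufficiently powered to precisely estimate a potential risk from waiving anti-biotic treatment" does not decide the matter. The only powered quantity is the difference in failure rates, which already has its interval, so the sentence cannot be read as a promise about serious adverse events.

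A reader might go further and infer that events are compared only as totals, so that antibiotic harm ("mainly reflected by gastro-intestinal complications such as diarrhoea, often caused by C. difficile") and harm from withholding would cancel. The documents do not support this. The Safety paragraph says neither total nor only. Intensive care, ventilatory support and vital status are listed apart, and relapse, exacerbation and cure are separate endpoints. Rates can be chosen so that totals match, but the article supplies no such rates, and its cited evidence points the other way: "The overall incidence of adverse events was higher in the antibiotics groups (Peto OR 1.53; 95% CI 1.03 to 2.27".

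**Conclusion.** The point holds in a narrow form. The one between-arm safety method that the article names is a test of difference. It cannot show that withholding antibiotics does no relevant harm, and it gives no upper limit on the excess risk of placebo.

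The power of about 25% and 44% rests on 480 per arm, equal allocation and assumed event rates. At commoner rates or larger differences the test does better, but non-significance still does not bound the risk.

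No stated figure is wrong and no two sections contradict each other. It is not established that harms will offset each other, or that the investigators intend to infer safety from a p-value. The absence of a breakdown of adverse events by type is not a finding either. The point is minor and cheap to correct.

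**What to change.** In the Safety paragraph, replace the chi-square test, or accompany it, with risk differences (placebo minus antibiotic) and two-sided 95% confidence intervals. Use score or exact intervals where events are rare. Cover adverse events, serious adverse events and the remaining key safety criteria: need for intensive care, need for ventilatory support, and death. Add one sentence saying that safety is judged from the interval limits and that a non-significant test is not evidence of safety.

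The cost is wording and a few more tables, since these events are already among the key safety criteria. The sample size does not change. The downside is presentational: the reported upper limits will look less reassuring than a non-significant p-value.

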### Statistical analysis

#### Efficacy/test accuracy

A patient is classified as a treatment failure if additional antibiotic therapy is required during treatment period or until the test of cure visit (TOC at day 30, primary endpoint).

The primary analysis will be stratified for centre. A two-sided 95%-confidence interval will be computed for the difference in failure rates for placebo minus experimental treatment group. The null-hypothesis of relevant inferiority of the placebo treatment will be rejected in favor of the alternative that antibiotic treatment is not required in this patient population, if the upper bound of the confidence interval does not exceed 10%, which is standard for the comparison of antibiotic treatments. The primary analysis will be conducted on the ITT-population including all randomized patients that have taken experimental drug or placebo at least once. A conservative rule will count missing values in the placebo-group with treatment failure, and as success in the active treatment group.

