### Study populations

We have calculated that 1300 patients have to be assessed for eligibility to have 980 patients to be allocated to trial. Ultimately 960 patients will be analysed. The total duration of the trial is calculated to be 36 months. Based on the feedback of the study centres of our research network we have calculated that 22 German centers need to be involved to guarantee adequate recruitment.

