The sample size of this trial is assumed to be sufficient to determine changes in relapse rates, time to relapse, clinical cure rates at EOT and TOC and to assess long-term consequences of sparing anti-biotic treatment.

This is a randomized and double-blind clinical trial with placebo matching tablets for active treatment. Block-randomization will be used. Randomization will be stratified for centre. All randomized patients that have received study medication at least once will be included into the primary intention-to-treat (ITT)-analysis. This is a non-inferiority trial and usually a per-protocol analysis would be used as primary analysis. However, the impact of potential missing values could be anti-conservative in the per-protocol analysis when demonstrating non-inferiority to placebo as well (pts with no improvement to placebo drop) and the ITT population is used here with a strategy that should maximize differences between treatment groups in case of uncertainty about outcome, because irrelevance of differences between treatment strategies is the objective to be demonstrated. In this complex situation missing values will be counted as failure in the placebo-group and as a success for patients in the antibiotics group. It is obvious that all attempts have to be undertaken to follow all patients to the end of the study.

In conclusion we believe that ABACOPD will be the first sufficiently powered double-blind placebo-controlled study in the field to systematically assess the question whether antibiotics, known to increase antibiotic resistance, are really needed in a well-defined patient cohort receiving state-of-the art treatment in all other aspects.

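### Adverse events are compared with a plain chi-square test although randomisation and the primary analysis are stratified by centre; a centre-stratified comparison would be a small, free improvement

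*Protocol article*

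**What the plan says.** In the Protocol article, the Safety paragraph of the statistical section has adverse events and serious adverse events summarised by arm and "descriptively compared between treatment-groups with a Chi-Square test". It names no strata, significance level, hypothesis or decision rule.

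The Discussion describes the allocation: "Block-randomization will be used. Randomization will be stratified for centre". The section Efficacy/test accuracy carries that design into the main comparison: "The primary analysis will be stratified for centre".

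The abstract (Methods/Design) gives the setting: "A total of 980 patients with moderate acute exacerbations will be included in 22 German centers". It adds that these centres are both hospitals and private practices. No adverse-event rate and no figure for variation between centres is given anywhere.

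**The concern.** Blocked randomisation within centre keeps the arms close to balanced in every centre. A centre that records many adverse events therefore adds about equally to both arms, and its high level drops out of the arm difference. The plain chi-square test does not use this. It computes its variance from the pooled event rate, and that variance includes the spread between centres. If the spread is real, the standard error is somewhat too large and the p-value somewhat too high.

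Hospitals and private practices could well differ in patient mix and in how fully they record events, so some spread is plausible. The comparison is also of interest. The Background cites more adverse events on antibiotics (Peto OR 1.53) and argues that patients may be spared them. At stake is a little precision in a descriptive safety comparison that the design already makes available.

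**Working it through.** **Anchor.** The article gives no figure for the safety comparison. Its own sample size reproduces: n = (1.960 + 1.282)² × 2 × 0.65 × 0.35 / 0.10² = 10.507 × 0.455 / 0.01 = 478.1, so 479 per group as stated. A trial of 980 patients in 22 centres is therefore the right frame (980 / 22 = about 45 per centre).

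**Inputs from the article.** 980 patients, 22 centres, blocks within centre, and odds ratios of 1.53 (any adverse event) and 2.62 (diarrhoea) from the Background.

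**Assumptions, because the article gives none.** Block size 4; two-sided 5% level; event rate on placebo 5%, 20% or 35%; normal centre effects on the log-odds with SD 0 to 1.0.

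**Closed form.** Let p be the mean event rate and λ the share of the pooled variance that lies between centres:

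λ = Var(centre rates) / [p(1 − p)], roughly SD² × p(1 − p) for a log-odds SD.

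The plain test then behaves as if its critical value were 1.96 / √(1 − λ). Its actual level is 2[1 − Φ(1.96 / √(1 − λ))]. Where the stratified test has 80% power (1.96 + 0.84 = 2.80), the plain test has Φ(2.80 − 1.96 / √(1 − λ)).

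| Rate p | SD | λ | Critical value | Level | Power (stratified = 80%) |
|---|---|---|---|---|---|
| 20% | 0.5 | 0.25 × 0.16 = 0.040 | 2.000 | 4.5% | 78.8% |
| 20% | 0.8 | 0.64 × 0.16 = 0.102 | 2.069 | 3.9% | 76.8% |
| 5% | 0.5 | 0.25 × 0.0475 = 0.012 | 1.972 | 4.9% | 79.7% |
| 5% | 0.8 | 0.64 × 0.0475 = 0.030 | 1.990 | 4.7% | 79.1% |

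The factor p(1 − p) is why rare events lose so little. The approximation overstates λ somewhat when the SD is large.

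**Simulation** (20,000 trials per setting; plain chi-square against Cochran-Mantel-Haenszel, CMH, neither with continuity correction; losses from unrounded values):

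| Placebo rate, OR | SD | Power, chi-square | Power, CMH | Loss (points) |
|---|---|---|---|---|
| 20%, 1.53 | 0 | 80.5% | 80.4% | none |
| | 0.3 | 79.7% | 80.1% | 0.4 |
| | 0.5 | 77.7% | 78.9% | 1.1 |
| | 1.0 | 68.0% | 72.9% | 4.9 |
| 35%, 1.53 | 0 | 90.2% | 90.3% | none |
| | 0.5 | 87.4% | 88.7% | 1.2 |
| | 1.0 | 79.1% | 84.2% | 5.1 |
| 5%, 2.62 | 0.5 | 97.8% | 97.9% | 0.1 |
| | 1.0 | 95.9% | 96.4% | 0.5 |
| 5%, 1.53 | 0.5 | 34.3% | 34.8% | 0.5 |
| | 1.0 | 31.0% | 33.2% | 2.2 |

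For common events the actual level of the chi-square test is about 4.4% to 4.8% at SD 0.5. At SD 0.8 it is about 3.7% to 4.1%, with a power loss of about 3 points. Unequal centre sizes change little (20% rate, SD 0.5: 77.2% against 78.2%).

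**Cross-check on the probability scale.** Take 22 patients per arm per centre, a mean rate of 40%, and centre rates with SD 10, 15 or 20 points. Then λ = 0.01 / 0.24 = 0.042, 0.0225 / 0.24 = 0.094 and 0.04 / 0.24 = 0.167. Simulated levels of the plain test are 4.7%, 4.0% and 3.4%. Power for a 9-point difference is 81.0%, 81.6% and 82.5%, against 82.3%, 84.0% and 86.5% with CMH. At a 5% rate with SD 3 points, power for a 4-point difference is 68.4% against 68.8%.

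**The case against.** The strongest reply is that nothing here is an error. The comparison is labelled descriptive, and no threshold or decision is attached to it. Crude per-arm safety tables are usual and easy to read. That the test is unstratified is inferred from silence in a condensed article, and the full protocol or analysis plan may say more. All of this stands, and it limits the weight of the point. It does not remove it: the article names a specific test, a plain chi-square test is naturally read as unstratified, and it sets aside strata that the same article uses for the primary endpoint.

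A reader might go further and infer that the safety comparison is conservative as a matter of fact, or that the trial would miss harm because of it. The documents do not support that. The effect needs between-centre variation that they do not report, and without it there is no loss. With a fixed risk difference, the power of the plain test does not even fall as centres diverge (81.0% to 82.5% above); the stratified test simply gains.

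A reader might also take a demonstration of more adverse events on antibiotics to be a trial objective. Under Objective, the primary aim concerns the failure rate and the secondary aims concern relapse, prolonged symptoms and cure. The excess of adverse events is background.

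A last objection is that stratifying rare events over 22 centres has its own cost. For the test this does not hold. A centre without events adds nothing to the numerator or the variance of CMH, and the simulations show no loss beyond noise at SD 0 or at a 5% rate. A stratified risk-difference interval does become sparse with few events, which is one reason to keep the crude counts.

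**Conclusion.** The point holds as a minor, optional improvement. If adverse-event rates differ between centres, the plain chi-square test is slightly conservative. It gives up about 1 point of power for common events at a log-odds SD of about 0.5 and about 3 points at 0.8. For rare serious events the loss is close to nil, and without centre variation there is none. Only at SD 1.0 with common events does it reach about 5 points.

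These sizes rest on assumed event rates, block size, test level and centre variation. The direction follows from the stated design. Validity is not threatened, since any error is on the conservative side, and the non-inferiority conclusion rests on the centre-stratified confidence interval for failure rates.

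**What to change.** In the Safety paragraph, keep the crude per-arm summaries and replace the chi-square test. Suggested wording: *The proportions of patients with at least one adverse event, and with at least one serious adverse event, will be compared descriptively by a Cochran-Mantel-Haenszel test stratified by centre, with a centre-stratified risk difference and 95% confidence interval. The centre strata are those of the primary analysis.*

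The serious-event comparison is included for consistency; little precision is gained there. The change also supplies an effect estimate, which a chi-square p-value does not.

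The cost is one sentence and no new data. Very small centres may need pooling, but the stratified primary analysis has to settle that in any case. If the full protocol or analysis plan already stratifies this comparison, no change is needed there.
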